### **3.1.3 Development of intervention**

Prior to the training, the researcher will develop the training curriculum as mentioned above. The research will present the training curriculum to the panel of experts in the ICF and training. The training curriculum will be tested as part of the feasibility study in the selected district hospital. The implementation strategy will be informed by the results from the feasibility study.

### **3.1.4 Procedure**

The following steps will be taken in carrying out the feasibility study:

Ethical approval will be sought from the University of Cape Town Institutional Review Board. For carrying out the study in Rwanda, the approval will be sought from National Health Research Committee (NHRC), and Rwanda National Ethics Committee (RNEC). The study will also need permission from the hospital. Conveniently, the researcher will, one by one, meet the health care professional who fulfils the inclusion criteria for giving him/her a participant information letter, and those who will agree to participate will sign a written consent for agreement. This will avoid any unnecessary pressure to take part in the study. For reviewing patients' records for baseline data, the written consent will also be requested from the hospital superintendent, because patients will not be available during data collection, so permission of getting their records will be sought from the hospital superintendent. It will not be possible to obtain consent from individual patients to access

their records that have been discharged six months prior to the commencement of the study, provided that these participants will be no longer receiving care from the hospital. In their study, Zegers et al. (2007) reviewing patients records in Dutch hospital, the hospital superintendents have been consented to have access to patients records. After the intervention (training), the permission to access their folders will be requested from patients or parents/guardians. This will be done either on admission, or if not possible due to the condition of the participants, during their hospital stay. The training will be two full days and the researcher will be the one to carry out the training.

Prior to the training, the researcher will explain the title, aims, objectives, rationale and potential benefits and risks of the study. Written consent will be requested from health professionals before training. After agreement to participate in the feasibility study, the pre-test measurement will be performed.

Power point presentations will be used during training. The majority of medical professionals in Rwanda have been trained and use English in their daily practice. For keeping the original content of the training, the presentation will be in English and, if it will be needed, the researcher will explain in local language (Kinyarwanda) or in French for more clarity. The training will be participatory; the trainees will be allowed to raise their opinions and questions at any time. Small group discussions and case presentations will be used during the training. After a case study, the practice will be done on the patients records' for demonstration. After training, the post-measurement of knowledge and attitudes on interprofessional practice will be performed in addition with training satisfaction questionnaire.

The training will be followed by a meeting between researcher and participants. The aim of the meeting will be to reach consensus on the training content, organisation, and training procedure and materials used in the training. In addition, the most appropriate methods to introduce the ICF conceptual framework into the routine management of patients within district hospitals will be identified. The meeting will also amend the outcomes measures.

The completed questionnaires will be deposited in the provided box that will be in the safe place within the hospital. After one week the researcher will collect the questionnaires from the box. The researcher will be also collecting discharge data from the medical records in orthopaedic/surgical, medical and paediatric wards. After collecting data, the researcher will organise the data for entry in the computer. After data entry and cleaning, the researcher will do data analysis.

Once the feasibility study has been conducted and the intervention has been finalised, the details of the intervention and amended informed consent documents will be submitted as an amendment for approval to the Faculty of Health Sciences Human Research Ethics Committee (HREC).

### **3.1.5 Data analysis**

Data analysis will be performed using STATISTICA. Descriptive statistics will be used to describe the characteristics of health professionals, such as frequency and percentage, mean and standard deviation. Within-group analysis will be used. The dependent t-Test will be used to compare the means before and after intervention (training) to detect whether there are any statistically significant differences between two means. Data will be presented in forms of tables, Scatterplots, and graphs. The ICC for absolute agreement between the two raters' scores of the audit of patient records will be used to determine the reliability of the scoring. The accuracy of interpretation of folders will be indicated by a set of ten folders of patients discharged longer than 6 months ago, assessed by researcher and research assistant (s), Data entered and compared, discussion and consensus reached. A further 10 files assessed and this process will continue until 80% agreement is reached.

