### **2.2.4 Validity and Reliability of the instruments**

If a study will need to develop a new questionnaire, this must be piloted and validated in order to check whether it is measuring what it is supposed to measure (validity) and is it doing it consistently (reliability) (Chiaburu & Lindsay, 2008). This will be considered in this study, as it will involve developing new instruments in order to monitor appropriateness of the content, wording of questions, type and form, level of sophistication of language, sequence and how is data sought from the respondents. After development of the questionnaires, validity and reliability will be assured. A sample of 50 health care professionals and 100 patients' records will be sufficient to ensure validity and reliability of the instruments. According to the Institute of Health and Care Research (2010), a sample size of at least 50-100 participants is required to ensure the validity and reliability. The folders will be assessed until the raters of folders can do it reliably. Example: If there is 80% agreement after 20 folders, there is no need to continue. If not, the number will be increased.

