### **3.1.2 Population and sampling**

The population for the study will include Medical doctors (General Practitioners), Physiotherapists, Mental Health/Clinical psychologist, Nurses, Social Worker, nutritionist/dietetic working in one selected District hospital (Nyamata hospital). Patients' records for discharged patients will also be included in the study. A purposive sampling method will be used in selecting the hospital, in that the hospital authorities must be ready and willing to participate in this feasibility study. A sample of convenience will be used with regard to health professionals and patients' records under the study.

As generalisability of the results is not required, the study will use a sample of convenience and recruit all eligible staff members who wish to take part in the study; and records of 100 patients on discharge will be recruited to test the feasibility, validity and reliability of the outcome measures.

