## 5.6 Appendix vi: International Classification of Functioning Disability and Health (ICF) checklist

One form will be completed for each patient record. Please place a sign ☒ in the box to indicate a positive response (only **one (1)** answer per statement).

| Activity Limitation & Participation Restriction                         |                          |                          |
|-------------------------------------------------------------------------|--------------------------|--------------------------|
| d1. LEARNING AND APPLYING KNOWLEDGE                                     | Yes                      | No                       |
| d110 Watching                                                           |  |  |
| d115 Listening                                                          |  |  |
| d140 Learning to read                                                   |  |  |
| d145 Learning to write                                                  |  |  |
| d150 Learning to calculate ( arithmetic )                        |  |  |
| d175 Solving problems                                                   |  |  |
| d2. GENERAL TASKS AND DEMANDS                                           |                          |                          |
| d210 Undertaking a single task                                          |  |  |
| d220 Undertaking multiple tasks                                         |  |  |
| d3. COMMUNICATION                                                       |                          |                          |
| d310 Communicating with -- receiving -- spoken messages                 |  |  |
| d315 Communicating with -- receiving -- non-verbal messages             |  |  |
| d330 Speaking                                                           |  |  |
| d335 Producing non-verbal messages                                      |  |  |

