| d820 School education                                                                 |  |  |
| d830 Higher education                                                                 |  |  |
| d850 Remunerative employment                                                          |  |  |
| d860 Basic economic transactions                                                      |  |  |
| d870 Economic self-sufficiency                                                        |  |  |
| d9. COMMUNITY, SOCIAL AND CIVIC LIFE                                                  |                          |                          |
| d910 Community Life                                                                   |  |  |
| d920 Recreation and leisure                                                           |  |  |
| d930 Religion and spirituality                                                        |  |  |

|                                            |                          |                          |
|--------------------------------------------|--------------------------|--------------------------|
| d940 Human rights                   |  |  |
| d950 Political life and citizenship |  |  |

| Environmental Factors                                                                       |                          |                          |
|---------------------------------------------------------------------------------------------|--------------------------|--------------------------|
| e1. PRODUCTS AND TECHNOLOGY                                                                 | Yes                      | No                       |
| e110 For personal consumption ( food, medicines )                                    |  |  |

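### Training of the record auditors stops at 80% agreement, with no stated unit and no chance correction, so at low tick rates raters who share no ticked ICF item could meet it

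*Combined protocol and SAP*

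**What the plan says.** Two places in the combined protocol and SAP set the rule for ending rater training on the record audit. Section 3.1.5 starts with "a set of ten folders of patients discharged longer than 6 months ago", scored by the researcher and the research assistant(s), then compared and discussed to consensus. It continues: "A further 10 files assessed and this process will continue until 80% agreement is reached". Section 2.2.4 gives the same threshold as an example: "If there is 80% agreement after 20 folders, there is no need to continue". If the threshold is not met, more folders are added.

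Section 3.1.5 also names a second statistic: "The ICC for absolute agreement between the two raters' scores of the audit of patient records will be used", for the purpose of determining how reliable the scoring is. It gives no minimum value and no action if the value is low.

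The folders come from the feasibility hospital, where "records of 100 patients on discharge will be recruited to test the feasibility, validity and reliability of the outcome measures" (section 3.1.2).

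The audit uses two forms. Appendix v has 30 items. Its items 17 and 18 carry over, as counts, the number of functioning and environmental items found with Appendix vi. Appendix vi is a list of Yes/No boxes in two parts, "Activity Limitation & Participation Restriction" and "Environmental Factors". Section 3.2.2.2 makes the comprehensiveness of records, measured by scores, part of the primary outcome. Section 4 assigns the main-trial audit to one blinded, trained research assistant and states no agreement standard for that person.

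**The concern.** Raw percent agreement gives full credit for boxes that both raters leave empty. On a long list where few boxes are ticked, shared blanks can carry the figure past 80% even if the raters never find the same content. The plan gives some reason to expect few ticks: the Problem Statement (section 1.2) describes assessment in Rwanda as centred on the disease or impairment, while Appendix vi lists only activity, participation and environmental items. The rule is also rechecked in batches until it is met, so a narrow failure can become a pass by repetition.

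The audit score is part of the primary outcome, and section 3.2.2.2 expects a small effect. Section 4 describes one auditor and no double rating during the trial, and the double entry in section 4.1 checks typing only. Rater training is therefore the main safeguard on how this outcome is measured.

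**Working it through.** The 80% is a chosen criterion with no derivation, so there is no figure to reproduce. The check is what the criterion lets through under each reading of its unit.

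**Inputs**
- Threshold 80%, batches of ten (sections 2.2.4 and 3.1.5); 100 feasibility records, so at most ten batches (section 3.1.2).
- Appendix vi, counted by chapter: functioning 6+2+5+6+7+4+7+6+5 = 48; environment 6+3+7+7+9 = 32; total 80.
- Appendix v: 30 items, of which 1–13 are consent and identification fields and 17–18 are the ICF counts.
- Share of items ticked: not given. Treated as an assumption and varied.

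**Reading 1: agreement per ICF item, no ticked item in common.** If each rater ticks k of 80 items, 2k boxes differ. Agreement is 1 − 2k/80, and chance agreement is p² + (1−p)² with p = k/80.

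| Ticks each | Share ticked | Raw agreement | Kappa | Result |
|---|---|---|---|---|
| 4 | 5% | 90.0% | −0.05 | pass |
| 8 | 10% | 80.0% | −0.11 | pass |
| 9 | 11.3% | 77.5% | −0.13 | fail |
| 16 | 20% | 60.0% | −0.25 | fail |
| 24 | 30% | 40.0% | −0.43 | fail |

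For 8 ticks, kappa = (0.80 − 0.82)/(1 − 0.82) = −0.11. Positive agreement is 0 in every row. If all 30 Appendix v items are added and agreed, the limit rises to 11 ticks each: 1 − 22/110 = 80%.

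**Reading 1 with independent random ticking.** Expected agreement p² + (1−p)² reaches 80% only for p up to 11.3%. The pass probability is the binomial chance of at least 640 agreements in 800 item pairs (10 folders × 80 items), treating items as independent. The ten-batch figure is 1 − (1 − b)^10, where b is the one-batch probability, assuming no learning between batches.

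| Tick rate | Expected agreement | Pass one batch | Pass within ten |
|---|---|---|---|
| 5% | 90.5% | 1.00 | 1.00 |
| 10% | 82.0% | 0.93 | 1.00 |
| 12% | 78.9% | 0.23 | 0.93 |
| 15% | 74.5% | 0.0002 | 0.0015 |

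**Reading 2: agreement on the 30-item Appendix v form.** This needs no tick rate. Raters who differ on items 17 and 18 in every folder and agree elsewhere score 28/30 = 93%. In general 80% of 30 is 24, so six items may differ. If items 1–13 are all agreed, six of the other 17 items (6/17 = 35%) can differ in every folder and the raters still pass.

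**Reading 3: whole folders must match.** Raters with no ticked item in common score 0% and fail. Under independence, matching all 80 boxes in 80% of folders needs per-item agreement of 0.8^(1/80) = 99.7%, a far stricter rule.

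**What the planned ICC would show.** Simulated two-way absolute-agreement ICC on tick counts (2,000 runs, 10 or 100 folders), with raw agreement near 90% throughout:
- independent ticking at 5%: median about 0;
- no shared item, unrelated counts: median about 0;
- no shared item, counts within one of each other: median about 0.92.

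The ICC catches raters whose counts are unrelated. It does not catch raters who reach similar counts from different items.

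**The case against.** A reader might infer that the rule can never fail on a form that is mostly No. The arithmetic does not support that: between 11.3% and 49% ticked the form is still mostly No, and raters with no shared item fail. The plan gives no tick rate, and the evidence for a low one is a single qualitative sentence. The unit is undefined, so the per-item reading is one of several. On the 30-item form, purely random raters would also fail: with 11 demographic items at 90.5% chance agreement and 19 at 50%, expected agreement is (11×0.905 + 19×0.5)/30 = 65%.

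A reader might also infer that shared blanks are the plan's evidence of reliability. Section 3.1.5 says otherwise: the ICC is the stated measure of scoring reliability, and the 80% rule is a calibration step. Nor does the text say that the main-trial auditor is certified by this rule. Section 3.1.5 concerns the feasibility study, and section 4 only says that the auditor is trained. The forms are not final either; sections 2.2.3 and 3.1.4 expect them to be developed and amended. And with one blinded auditor for both arms, poor detection would mainly cost precision or sensitivity rather than create an obvious difference between arms.

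All of that stands and limits the point. What it leaves untouched is that the only rule that ends training has no unit and no chance correction, that the better statistic has no minimum and no consequence, and that the person who scores the primary outcome has no stated standard. Section 2.2.4 sits in the general methodology, so the 80% rule may be meant to cover that person; if not, nothing does.

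**Conclusion.** The point holds in a limited form. The 80% rule gives little assurance under two plausible readings. Counted per ICF item, it passes raters with no ticked item in common when each ticks up to 8 of 80 items; from 9 ticks each it fails them. This rests on an assumed tick rate of about 10% or less. Counted on the Appendix v form, it passes raters who differ on both ICF counts in every folder (93%), with no assumption about tick rate. Under a whole-folder reading the weakness disappears.

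The documents do not support saying that the rule cannot fail, that unreliable auditors will be certified, or that the measurement error will go unmeasured, since an ICC is planned. The defect is that the ICC does not decide anything and the rule that does decide is undefined. It should be fixed before the feasibility ratings start.

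**What to change.** In sections 2.2.4 and 3.1.5, replace the 80% stopping rule with the absolute-agreement ICC that is already planned, in its single-rater form because one person audits the main trial. Compute it on the scores the trial will use: the item 17 count, the item 18 count and the final record score once the form is settled. State the minimum in advance, and say whether it applies to the estimate or to the lower confidence limit; the value is the investigators' choice.

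Compute the ICC with its confidence interval on folders rated independently after calibration and before any consensus discussion. Leave out the calibration rounds, and do not rely on whichever batch of ten first passes. Report positive agreement and kappa by section of the forms, because the ICC on counts cannot see agreement reached from different items; kappa is unstable when ticks are rare, so show both. Keep raw percent agreement as description, with its unit stated. In section 4, require the main-trial auditor to meet the same criterion before the baseline audit.

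The cost is protocol wording and possibly more double-rated folders, which section 2.2.4 already allows. As an illustration, suppose the lower 95% limit had to exceed 0.70. By the usual two-rater F approximation, 20 folders need an observed ICC of about 0.87: (1.70/0.30) × 2.53 = 14.3, and (14.3 − 1)/(14.3 + 1) = 0.87. With all 100 folders the figure is about 0.79: (1.70/0.30) × 1.49 = 8.4, and (8.4 − 1)/(8.4 + 1) = 0.79. Here 2.53 and 1.49 are the 97.5% points of F with 19 and 19, and 99 and 99, degrees of freedom.

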## **3.2 Methodology - Intervention study**

### **3.2.1 Study design**

A Cluster Randomised Control Trial (CRCT) using a pragmatic study design will be used in this study. Cluster randomised controlled trials (CRCTs), is a design used in health research services whereby clusters are randomised to intervention groups. This design is primarily used to avoid contamination between the control and experimental groups when a single setting (such as a ward) is utilised (Hemming, Girling, Sitch, Marsh, & Lilford, 2011). This design will be appropriate to compare the outcome of the intervention between the experimental and comparator group.

### **3.2.2 Population**

The population for the study will be the same as feasibility study. This will include the above mentioned health care professionals and patients' records of discharged patients. According to the reports from different hospitals, the average number of beds in each hospital is 182, Doctors (General practitioners) is 10, 80 Nurses, two Physiotherapists, one Mental Health/Clinical Psychologist, and one social worker. In general, these are the health professionals that may be found in District hospitals of Rwanda who have responsibility, at some extent, to provide services on the patients in above mentioned wards.

#### ***3.2.2.1 Inclusion criteria***

##### **Health professionals**

- Full time health professionals during the period of intervention and data collection.
- Qualified health care professional.
- Health care professional working either in Orthopaedic/surgical, medical and paediatric wards.
- Health care professional with at least 6 months of working experience in the above mentioned wards.

##### **Patients' records**

- Medical records of patients who have been admitted to the orthopedic/surgical, medical and paediatric wards for at least five days.
- Medical records of patients who have been discharged.

#### ***3.2.2.2 Sample size calculation***

It is anticipated that a 20% (8) sample of 40 district hospitals will allow the outcomes to be generalised to the other hospitals. In their study, Zegers et al. (2007) reviewing patients records in Dutch hospital, a random sample of 20% of the hospitals was selected and the results were

generalized. At each hospital all the relevant health professionals will be included in the training so the sample will be one of convenience. The primary outcome of this study will be the improved interprofessional practice within the district hospitals and comprehensiveness of the patients' records demonstrated by the scores. A sample size calculation will be done once the needed tools have been finalised and the mean and standard deviation calculated during a feasibility study. However as multi-level regression analysis will be done to account for the effect of clustering, a sample of 800 patients records (100 from each hospital) should allow for the analysis of at least 80 variables. This is a large number but, as it is anticipated that the effect size will be small due to the presence of so many confounding variables, a large sample size will be required to prevent a Type II error from occurring.

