## **2 Methodology – General**

### **2.1 Research setting**

The study will be carried out in Rwanda, specifically in district hospitals. Rwanda has 40 district hospitals covering four provinces plus four district hospitals in Kigali city (Government of Rwanda, MOH, 2013).

In general, apart from Kigali city, all district hospitals in Rwanda are similar in terms of patients and conditions, services, materials and equipment as well as health personnel, so the four hospitals from Kigali will not be part of this study. The district hospitals have both inpatient and outpatient services. Outpatient services include: general consultation, dentistry, laboratory, medical imaging, mental health, ophthalmology, HIV/AIDS unit, social welfare, and physiotherapy. Inpatient services includes: orthopaedic/surgical, medical, paediatrics, and maternity. This study will only recruit patients' records from inpatient services, specifically orthopaedic/surgical, internal medicine and paediatric. This choice is based on the fact that patients on these wards may be hospitalised for longer periods and receive treatment from different health professionals than those on other wards. The maternity ward will be excluded because the mothers generally spend only one to two days in hospital.

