### ***3.2.2.3 Recruitment and sampling method***

#### **District hospitals**

Cluster random sampling will be used by a blinded person to select the district hospitals within 40 districts of four provinces. It is anticipated that eight district hospitals will participate in this study. The sample will include Gahini hospital, Kiziguro hospital, Nemba hospital, Rutongo hospital, Remera Rukoma hospital, Nyanza hospital, Byumba hospital, and Ruhango hospital. The same individual will randomly allocate four hospitals on the experimental arm and other four hospitals on the comparator arm. The experimental hospitals will include: Gahini hospital, Nemba hospital, Rutongo hospital, and Remera Rukoma hospital. The comparator hospital will be composed of Kiziguro hospital, Ruhango hospital, Byumba hospital, and Nyanza hospital.

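### A 20% sampling fraction does not justify eight hospitals; random selection can support generalisation, but only with the precision of four hospitals against four, which the plan does not state

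*Combined protocol and SAP*

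**What the plan says.** Section 2.1 defines the frame: "Rwanda has 40 district hospitals covering four provinces plus four district hospitals in Kigali city", with the Kigali hospitals left out of the study.

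Section 3.2.2.2 takes eight of the 40 and gives its reason: "It is anticipated that a 20% (8) sample of 40 district hospitals will allow the outcomes to be generalised to the other hospitals". The support is a precedent. In a cited Dutch study "a random sample of 20% of the hospitals was selected and the results were" generalised. The title in the reference list shows that study to be a retrospective record review of how often adverse events occur, not a trial of an intervention.

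The same section adds that "a sample of 800 patients records (100 from each hospital) should allow for the analysis of at least 80 variables" and that "it is anticipated that the effect size will be small". It puts off the formal sample size calculation until the feasibility study has supplied a mean and standard deviation.

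On selection and allocation, Section 3.2.2.3 (District hospitals) says "Cluster random sampling will be used by a blinded person to select the district hospitals within 40 districts of four provinces", and then "The same individual will randomly allocate four hospitals on the experimental arm and other four hospitals on the comparator arm". The eight hospitals and their arms are already listed there.

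For analysis, Section 4.1 lists chi-square, Mann-Whitney and independent t-tests between the groups at each time point, and also multi-level regression to control for clustering. It does not say which of these carries the conclusion.

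**The concern.** The number of hospitals and the intended reach of the conclusions both rest on a proportion of the frame. The precision of an inference to other hospitals depends mainly on how many hospitals are studied and how much they differ, and hardly at all on what share of the frame they make up. A descriptive precedent that used the same share does not change that. It is also weak support for a comparison in which each condition is seen in only half the sampled hospitals.

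Nowhere do the documents give an ICC, a design effect or an interval width for four hospitals against four. A reader could therefore take the 20% as assurance that findings carry over to the other hospitals with useful precision. If the record-level tests in Section 4.1 were then used for the arm comparison, the reported intervals would support that belief wrongly, because they would treat 800 records as 800 independent units.

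**Working it through.** **The plan's own figures.** 8/40 = 20%. 8 × 100 = 800 records. 800/80 = 10 records per variable. All three reproduce. The documents state no power, significance level, ICC or numerical effect size, so there is no precision figure to reproduce.

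**Step 1: what the fraction does.** For a mean over k of N hospitals, looking at hospital variation alone and in units of the between-hospital SD, SE = √((1 − k/N)/k).

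| Held fixed | N | k | Fraction | SE |
|---|---|---|---|---|
| 8 hospitals | 20 | 8 | 40% | 0.274 |
| 8 hospitals | 40 | 8 | 20% | 0.316 |
| 8 hospitals | 80 | 8 | 10% | 0.335 |
| 8 hospitals | 400 | 8 | 2% | 0.350 |
| 20% | 20 | 4 | 20% | 0.447 |
| 20% | 40 | 8 | 20% | 0.316 |
| 20% | 80 | 16 | 20% | 0.224 |
| 20% | 400 | 80 | 20% | 0.100 |

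With eight hospitals, cutting the fraction from 20% to 2% moves the SE only from 0.316 to 0.350. With the fraction held at 20%, the SE runs from 0.447 to 0.100 as the count rises. At 8 of 40 the fraction enters only through √(1 − 0.2) = 0.894, about 11% off the SE.

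**Step 2: the contrast the trial estimates.** Inputs from the documents are 4 hospitals per arm and 100 records per hospital at each audit. Assumptions are an ICC of 0.01 to 0.20, a 95% interval, one follow-up occasion and no baseline adjustment. Results are in units of the total SD of the record score.

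- SE = √(2 × [ICC + (1 − ICC)/100]/4)
- Degrees of freedom = 8 − 2 = 6, so t = 2.447
- Half-width = 2.447 × SE
- Design effect = 1 + 99 × ICC
- Effective number of records = 800/design effect

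| ICC (assumed) | Design effect | Effective records | SE | 95% half-width |
|---|---|---|---|---|
| 0.01 | 1.99 | 402 | 0.100 | 0.24 SD |
| 0.05 | 5.95 | 134 | 0.172 | 0.42 SD |
| 0.10 | 10.9 | 73 | 0.233 | 0.57 SD |
| 0.20 | 20.8 | 38 | 0.322 | 0.79 SD |

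**Step 3: the record-level reference.** Treating the records as independent, 400 per arm, the half-width is 1.96 × √(2/400) = 0.14 SD. The hospital-level interval is wider by a factor of about 1.8 at ICC 0.01 (0.244/0.139), 3.0 at 0.05 (0.422/0.139) and 5.7 at 0.20 (0.789/0.139).

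**Step 4: two checks on the size.** Step 2 leaves out the finite-population correction. Applying it in full at ICC 0.05 would give 0.422 × 0.894 = 0.38 SD, so the fraction does not rescue the precision. Nor do more records: at ICC 0.05 with unlimited records per hospital, the half-width is 2.447 × √(2 × 0.05/4) = 0.39 SD.

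**The case against.** The strongest reply is that generalisability is first a matter of how hospitals are chosen. Section 3.2.2.3 describes random selection from the frame, and that, if carried out, is a proper basis for inference to all 40. This stands. A reader might infer that the results cannot be generalised at all, and the documents do not support that. The fault is the fraction-based argument and the missing precision.

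A second reply is that Section 3.2.2.2 is hedged, defers the formal calculation, and relies on multi-level regression. This stands in part. The plan does not claim that 20% gives adequate power, and it does not ignore clustering. But the hospitals are already named and allocated. The deferred calculation is described in terms of a mean and SD from a feasibility study in one hospital, which cannot show how much hospitals differ. Multi-level regression can give honest intervals; it does not explain why eight hospitals suffice. Section 4.1 also leaves record-level tests open for the same comparison.

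Two further readings are tempting and should be resisted:

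- Section 2.1 says that "all district hospitals in Rwanda are similar in terms of patients and conditions". A reader might take this as support for the 20%. It is qualified as applying outside Kigali and is used to justify leaving the Kigali hospitals out.
- A reader might set the feasibility hospital against the stated averages to argue that hospitals are not similar: 14 doctors against 10, 3 physiotherapists against 2, 3 social workers against 1. Other figures are close: 79 nurses against 80, and 164 beds against 182. One purposively chosen hospital says little about spread either way.

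**Conclusion.** The point holds in this form: a 20% fraction and a descriptive precedent do not justify eight hospitals or the claim to generalise. Random selection can make inference to the 40 non-Kigali hospitals unbiased, but its precision is set by four hospitals against four. Under the assumed ICCs of 0.01 to 0.20, the 95% half-width for the arm difference is about 0.24 to 0.79 SD, against 0.14 SD if clustering is ignored.

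This matters because the plan itself expects a small effect. If that meant 0.2 SD (my assumption; the plan gives no number), even the narrowest of these half-widths would exceed it.

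The argument about the fraction needs no assumed ICC. The interval widths do rest on the assumed ICCs and on follow-up data alone. Baseline adjustment or use of the repeated audits could narrow them by an amount the documents do not allow one to calculate, but the number of hospitals would stay at eight.

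**What to change.** In Section 3.2.2.2:

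- Delete the 20% argument and the precedent.
- Rest generalisation on the random selection of hospitals from the 40 outside Kigali.
- State the expected 95% interval width for four hospitals against four over a stated ICC range, as in the table above. This also replaces the deleted sentence with an honest account of what eight hospitals can deliver.

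In Section 4.1:

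- Base the arm comparison on hospitals treated as random, with small-sample degrees of freedom (6 for the unadjusted contrast).
- State that record-level chi-square, Mann-Whitney and t-tests will not be used for that comparison.
- Limit any extension to the other 32 hospitals (40 − 8) to what those intervals allow.

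The cost is protocol wording, one short table and a small-sample setting in the planned model. No hospitals or records need be added. The downside is a less favourable statement of what the trial can conclude.
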